#### Data analysis plan

DTGT and STGT groups will be compared on baseline characteristics using Student *t*-tests for continuous data and Fisher’s exact test for proportions. The hypotheses will be tested using an intention-to-treat analysis, applying a repeated measures design whereby the two groups will be compared on primary outcomes at: (i) baseline, (ii) after the completion of the intervention, and (iii) 6 months following completion of the intervention. For the primary outcomes of dual-task effects on gait and cognition, a 2 x 3 mixed model repeated measures ANOVA with group (DTGT, STGT) as between-subjects factor and time (pre-training, post-training, 6-month follow-up) as within-subjects factor will be applied to DTE for each gait task separately (preferred walking, fast walking) and for each cognitive task separately (Stroop, clock). A similar analysis will be performed for all secondary outcome measures. Tukey’s honestly significant difference (HSD) post-hoc tests will be applied to examine the significant differences for all ANOVAs. If the normality assumptions for ANOVA are not supported, nonparametric equivalent statistical methods including Mann–Whitney *U*-tests and Wilcoxon signed-ranks tests will be used.

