### Interventions

The interventions will be implemented in the outpatient physical therapy clinic at New England Rehabilitation Hospital (Woburn, MA). Physical therapists trained in the study protocols will provide the intervention one-on-one. The two groups (DTGT, STGT) will each participate in a 30-minute training session, 3 times a week for 4 weeks (total of 12 sessions). A maximum of 6 weeks will be allowed to complete the 12 sessions. For participants in both groups, each session will begin with a 5–10 minute warm-up comprising lower extremity stretching, three 10-m walks at self-selected speed and three 10-m walks at fastest speed. The warm-up walks allow the therapist to observe single-task gait performance, (a) as a basis for focusing the goals of the session (e.g. increasing stride length), and (b) to establish a reference of single-task performance for the DTGT group.

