### Outcome measures

Primary and secondary outcome measures will be assessed at baseline, after 12 sessions of the intervention, and 6 months following completion of the intervention.

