### Data analysis

#### Sample size calculation

The study has been powered to detect a minimum difference of 10% in dual-task cost on gait speed between the DTGT and STGT groups. The difference of 10% is based on the established minimal clinically important difference for gait speed decline in older adults (including people with stroke). Perera et al.
[46] determined that a decline in gait speed of 0.1 m/s was associated with substantial meaningful change in physical function. Based on the expected mean gait speeds throughout the phases of this study, a dual-task decline of 0.1 m/s corresponds to a 10-12% dual-task cost on gait speed. Assuming within-group standard deviation of 10.15, with 80% power at the 0.05 significance level, we need 18 subjects in each group. Allowing for 20% attrition at the 6-month follow up, we plan to randomize 22 subjects to each group (total 44 subjects).

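### The analysis is called intention-to-treat, but the named three-occasion repeated measures ANOVA, fitted in the usual way, keeps only participants with all three visits, and both follow-up visits are timed from finishing the 12 sessions

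*Protocol article*

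**What the plan says.** Four parts of the protocol article bear on this point.

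- **Data analysis plan, population.** "The hypotheses will be tested using an intention-to-treat analysis, applying a repeated measures design". Intention-to-treat is not defined further.
- **Data analysis plan, model.** The primary outcomes are analysed by "a 2 x 3 mixed model repeated measures ANOVA with group (DTGT, STGT) as between-subjects factor" and "time (pre-training, post-training, 6-month follow-up) as within-subjects factor". Tukey's HSD follows, and Mann–Whitney and Wilcoxon signed-ranks tests are the fallback if normality fails.
- **Outcome measures.** Outcomes are "assessed at baseline, after 12 sessions of the intervention, and 6 months following completion of the intervention". Under Interventions: "A maximum of 6 weeks will be allowed to complete the 12 sessions".
- **Sample size calculation.** The trial is "powered to detect a minimum difference of 10% in dual-task cost on gait speed", with a within-group SD of 10.15, 80% power and a 0.05 significance level, giving 18 per group. Then: "Allowing for 20% attrition at the 6-month follow up, we plan to randomize 22 subjects to each group".

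The article does not say how a participant with a missing occasion enters the model. It also does not say when a participant who stops before 12 sessions is assessed.

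**The concern.** An intention-to-treat comparison should use everyone randomised, as far as their data allow. A classical split-plot ANOVA needs a complete row for each person, so one missing occasion removes the other two. The post-training comparison needs no 6-month data, yet it would be made only in people who returned at 6 months.

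Visit timing raises a separate problem that no choice of model can solve. If outcomes are collected only once the sessions are finished, data from those who stop early may never exist.

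What is at stake is the randomised comparison. Participants know their allocation, and dual-task training adds a cognitive task to 75% of repetitions, so loss could plausibly differ between arms. If poor responders leave one arm more than the other, the remaining participants in that arm look better than the arm as randomised.

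**Working it through.** **1. The plan's own sample size.** Inputs from the Sample size calculation: difference 10, SD 10.15, 80% power, alpha 0.05 (taken as two-sided). The standardised difference is 10/10.15 = 0.985. The two-sample t-test needs 17.19 per group, rounded up to 18, which reproduces the stated figure. The step to 22 matches 18 × 1.2 = 21.6, rounded up.

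**2. Complete cases at the planned attrition.** 44 × 0.8 = 35.2, or 17.6 per group. Power by t-test is about 81% with 17.6 per group and about 89% with 22, so power remains at the design level.

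**3. Precision at post-training if loss is random.** The standard error of the difference is SD × √(2/n).
- All 22 per group: 10.15 × √(2/22) = 3.06.
- 17.6 per group (20% loss): 10.15 × √(2/17.6) = 3.42.
- About 17.4 per group (21% loss): 3.44.

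The ratio is √(1/0.8) = 1.118 at 20% loss and 3.44/3.06 = 1.124 at 21%. The standard error is about 12% larger, with no bias.

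**4. Bias at post-training if loss depends on outcome.** Everything in this step is assumed, because the protocol gives no dropout pattern. Let z be the standardised post-training value, and let the probability of staying be Φ(a + bz). The mean of those who stay is then shifted by SD × [b/√(1+b²)] × φ(q)/Φ(q), where q = a/√(1+b²) and Φ(q) is the proportion kept. The bias in the difference is the shift in DTGT minus the shift in STGT.

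Severe case: a = 0.8 and b = 1.2 in DTGT, with random loss of 12% in STGT. Then q = 0.8/1.562 = 0.512 and Φ(q) = 0.696, so 30.4% of DTGT is lost. The shift is 10.15 × 0.768 × 0.350/0.696 = 3.9, so a true difference of 10 is estimated as 13.9. With a correlation of 0.5 between visits, the 6-month shift is half that, about 2.0.

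| Assumed loss | Post-training bias |
|---|---|
| DTGT 30%, b = 1.2; STGT random | 3.9 |
| DTGT 30%, b = 0.6; STGT random | 2.6 |
| DTGT 30%, b = 0.3; STGT random | 1.5 |
| 20% in both arms, b = 0.3 to 0.5 in DTGT only | 1.0 to 1.6 |
| 30% vs 12%, b = 0.3 to 0.5 in both arms | 0.8 to 1.2 |
| Same rate and same b in both arms | 0 |

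These are biases in the difference between arms at the post-training visit. Selection also shifts the baseline mean of those kept, by the correlation times the post-training shift. The bias in change from baseline to post-training is therefore (1 − 0.5) × 3.9 = 2.0 in the severe case. For change from baseline to 6 months it cancels when both visits correlate equally with post-training. A simulation with no true effect, a common correlation of 0.6 and post-dependent loss in DTGT agreed: about 35 of 44 were kept, and the complete-case bias in that change was −0.01 (Monte Carlo error 0.18).

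**5. Visit timing.** The second assessment is set "after 12 sessions of the intervention, and 6 months following completion of the intervention", and the third counts from the same completion. For someone who stops at session 5, say, neither date is defined. The 6-week ceiling could serve as the anchor, but the text does not use it that way.

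**The case against.** The strongest reply is that listwise deletion is nowhere stated. The term mixed model could mean a likelihood model that keeps incomplete cases, and a condensed article may leave missing-data handling to a full protocol or analysis plan that is not shown. This stands in part: silence on missing data is not the finding, and deletion is an inference. It is a strong one, because the 2 x 3 layout, the between/within factors, Tukey's HSD and the reference to ANOVA assumptions all describe the classical procedure. The point concerns a stated label and a stated model that do not fit together.

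Three stronger readings are tempting, and the document does not support them.

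- **The step from 18 to 22 confirms listwise deletion.** It does not. Inflating for attrition is routine under any model, since people lost at 6 months provide no 6-month value.
- **The trial will be an analysis of completers with a fifth lost.** The 20% is a planning allowance for loss at 6 months. It is neither an observed loss nor a rate of failing to finish 12 sessions, for which the protocol gives no figure.
- **Participants who stop early are excluded.** Nothing says so, and the intention-to-treat statement points the other way. Their visit dates are simply undefined.

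The 3.9-point bias also rests on a severe assumption: a DTGT participant 1 SD below the mean drops out with probability about 66%, and one 1 SD above with about 2%. Milder mechanisms give much less.

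**Conclusion.** The point holds in a conditional form. Fitted in the usual way, the named ANOVA does not deliver the intention-to-treat analysis that the plan promises. It would keep about 35 of 44 at the planned attrition and discard post-training data already observed. Separately, the visit definition leaves early stoppers without an outcome date, which undermines intention-to-treat under any model.

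The harm is possible bias and wasted post-training data, not a shortfall in power. Under random loss the cost is a standard error about 12% larger. Under outcome-dependent loss that differs by arm, the post-training difference could be off by about 1 to 4 points, and by about half that in change from baseline at a correlation of 0.5. The dropout rates, their dependence on outcome and the correlation are all assumed, and the bias could favour either arm. The effect of the visit-timing gap cannot be sized, because the protocol gives no rate of early stopping.

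**What to change.** 1. In the Data analysis plan, state that the primary model is a likelihood-based linear mixed model with group, time and group-by-time, using all available measurements from every randomised participant.
2. In Outcome measures, schedule the outcome visits for all participants by calendar time, at the end of the 6-week training window and 6 months later, regardless of sessions attended.

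A sensitivity analysis for data missing not at random is optional. It is worth considering because the mixed model removes the bias only where loss is explained by the observed values.

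The first change costs only wording. The second needs one sentence and some effort to bring back participants who stopped training. It has to be settled while those visits can still take place, because no later analysis can recover outcomes that were never collected.

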### Randomization and blinding

Following baseline evaluation, the participants will be randomized to either DTGT or STGT using a 1:1 randomization sequence prepared by the study biostatistician. Group assignment will be concealed using opaque envelopes, which will be opened after the completion of the baseline assessment. Research personnel conducting the baseline, post-intervention, and follow-up assessments will be blind to group assignment. The investigator processing the data extracted from activity monitoring will also be blind to group assignment. Participants will be aware of their group allocation, but will be naïve to the study hypotheses. Therapists providing the study interventions cannot be blinded in this study design.

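### The primary 2 x 3 ANOVA treats baseline DTE as an outcome visit instead of a covariate, so the DTGT-STGT comparison is less precise than the collected data allow

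*Protocol article*

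**What the plan says.** The Data analysis plan section specifies "a 2 x 3 mixed model repeated measures ANOVA with group (DTGT, STGT) as between-subjects factor", with "time (pre-training, post-training, 6-month follow-up) as within-subjects factor will be applied to DTE for each gait task separately", and likewise for each cognitive task. Baseline is also listed among the occasions of comparison: "the two groups will be compared on primary outcomes at: (i) baseline, (ii) after the completion of the intervention". No covariate appears, and nothing constrains the two groups to a common baseline mean. The same approach is carried to the other endpoints: "A similar analysis will be performed for all secondary outcome measures".

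The data needed for adjustment are collected. The Outcome measures section gives the schedule: "Primary and secondary outcome measures will be assessed at baseline, after 12 sessions of the intervention, and 6 months following completion of the intervention". The Randomization and blinding section gives the order of events: "Following baseline evaluation, the participants will be randomized to either DTGT or STGT using a 1:1 randomization sequence prepared by the study biostatistician". Baseline DTE is therefore a genuine pre-randomization measurement.

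The Sample size calculation section says the study is "powered to detect a minimum difference of 10% in dual-task cost on gait speed between the DTGT and STGT groups". It uses one SD and no correlation between visits, so it takes no credit for baseline.

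**The concern.** Once baseline is a level of the time factor, the model offers three ways to read a treatment effect. Each uses the baseline value less well than a covariate would.

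- **Group-by-time interaction.** This is the natural test. It compares changes from baseline with the slope on baseline fixed at 1.
- **Group main effect.** This averages over the pre-training visit, where randomization makes the expected difference zero, and so dilutes any real effect.
- **Post-hoc comparison of groups at one visit.** This does not use baseline at all.

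The trial is small: 44 randomized and about 18 per group expected at 6 months. A chance difference in baseline DTE is likely. Given such a difference, the change contrast over-corrects it (regression to the mean), while the main effect leaves much of it in. At stake is the width of the interval for the contrast on which the trial was sized.

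**Working it through.** **Inputs.** From Sample size calculation: difference 10, SD 10.15, 80% power, significance level 0.05 (sidedness not stated; two-sided assumed), 18 evaluable and 22 randomized per group. Assumed: equal variance at each visit and a baseline-to-follow-up correlation rho, which the protocol does not give.

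**The plan's own figure.** A two-sample t-test by noncentral t has power 79.5% at 17 per group and 81.9% at 18. The stated 18 per group reproduces.

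**Precision at one follow-up visit.** The standard error (SE) without baseline is 10.15 x sqrt(2/18) = 3.38. In units of that variance:

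- follow-up value only: 1
- change from baseline: 2(1 - rho)
- baseline as covariate (ANCOVA): 1 - rho²

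Since 2(1 - rho) - (1 - rho²) = (1 - rho)², the covariate version has the smaller variance for every rho below 1. The ratio of change to ANCOVA variance is 2/(1 + rho). Against this, ANCOVA pays one degree of freedom and a small cost for estimating the slope.

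**Power for 10 points at 18 per group** (noncentral t; ANCOVA with one fewer degree of freedom):

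| rho | SE, change | SE, ANCOVA | variance ratio | power, change | power, ANCOVA |
|---|---|---|---|---|---|
| 0.3 | 4.00 | 3.23 | 1.54 | 68% | 85% |
| 0.4 | 3.71 | 3.10 | 1.43 | 75% | 88% |
| 0.5 | 3.38 | 2.93 | 1.33 | 82% | 91% |
| 0.6 | 3.03 | 2.71 | 1.25 | 89% | 95% |
| 0.7 | 2.62 | 2.42 | 1.18 | 96% | 98% |

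Simulation (20,000 runs) gives 68.1% against 84.2% at rho 0.3, 81.5% against 90.2% at 0.5, and 95.8% against 97.6% at 0.7. With all 22 per group at rho 0.5, the closed form gives 89% against 96%.

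**The overall interaction F test** (2 df, both follow-up effects equal to 10, 10,000 simulated runs) has power 72%, 86% and 98% at rho 0.3, 0.5 and 0.7. ANCOVA on the mean of the two follow-ups has 97%, 98% and 99.7%.

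**The group main effect**, if read as the treatment test: the expected difference is (0 + 10 + 10)/3 = 6.7 and the variance is SD²(1 + 2 rho)/3. At rho 0.5 and 18 per group, power is 65%.

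**Chance imbalance.** With 22 per group, the SE of the baseline difference is 10.15 x sqrt(2/22) = 3.1. An imbalance of 3 points or more therefore arises in about one trial in three. Given a 3-point imbalance and rho 0.5, the change contrast is shifted by (0.5 - 1) x 3 = -1.5 points and the main effect by 3 x (1 + 2 x 0.5)/3 = +2 points. Adjustment on baseline has no such conditional shift.

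**The case against.** The strongest reply is that nothing in the plan is invalid. Under randomization the interaction contrast is unbiased and its type I error is unaffected. The over-correction exists only conditional on an observed imbalance. This stands, and the point is about precision alone.

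The gain also depends on a correlation nobody has stated. At rho 0.5 or above, the planned single-visit contrast already reaches 80% power with 18 per group, and at 0.7 the gain is about 2 points. At post-training, before the allowed 6-month attrition, numbers may be nearer 22 per group; there the comparison is 94.6% against 97.9% at rho 0.6. The closed form also flatters ANCOVA slightly: simulations put the gain at rho 0.6 at 4.6 to 4.8 points, not 5.4. All of this stands as a limit on size. But since rho is unknown, it supports the method that does not lose when rho is low. Below 0.5 the change contrast does worse than ignoring baseline.

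The single-visit comparison is not the 2-df F test the plan names. That is true, but for a sustained effect the F test also has less power than a baseline-adjusted analysis. Nor does the plan name the group main effect as its treatment test; that calculation matters only if someone reads it so, and the severity does not rest on it.

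Finally, the Background and Discussion sections ask about automatization of gait and about change over time, which call for within-group change. That can be reported descriptively, or kept in a longitudinal model with a common baseline mean. It does not require the planned ANOVA as the between-group test.

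**Conclusion.** The concern holds. The article itself fixes a primary model that uses baseline DTE inefficiently, and it gives no reason for the choice. For any rho below 1, the planned change contrast has 2/(1 + rho) times the variance of the baseline-adjusted one: a third more at rho 0.5, and 18% more at 0.7. In power at 18 per group, the closed-form gain is about 17 points at rho 0.3, 9 at 0.5, 5 at 0.6 and 2 at 0.7. These figures assume equal visit variances, a two-sided 0.05 test and the protocol's SD for gait-speed DTE. The variance ratio applies equally to cognitive DTE, for which no SD is given. The stated sample size is not shown to be wrong. The change should be made, but the trial is valid without it.

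**What to change.** Replace the 2 x 3 ANOVA as the primary between-group test. Take DTE at post-training and at 6 months as the outcomes in a linear mixed model with group, visit (two levels), group x visit, the baseline value of the same DTE, and baseline x visit. Report the baseline-adjusted DTGT-STGT difference with its 95% CI at each visit. If change from baseline within each group is to stay in the model, a three-visit longitudinal model with baseline means constrained equal is an acceptable alternative.

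Use the same form for secondary outcomes that have a baseline value. The falls diary starts only after the intervention, so falls would be handled separately. State that the group main effect of any model including the baseline visit will not be used as a test of treatment.

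The cost is one paragraph of wording, one or two degrees of freedom, and a simple rule for a participant without a baseline DTE, which should be rare because baseline precedes randomization. No added patients or measurements are needed.

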## Discussion

This single-blind randomized controlled trial will determine whether task-specific training in dual-task walking can reduce dual-task interference during gait, compared to single-task gait training. Preliminary studies provide promising evidence that dual-task gait training can improve dual-task gait performance after stroke
[17,18]; however, these small studies are limited by the lack of a control group and long-term follow-up. The results of this randomized controlled trial will provide insight into whether reductions in dual-task interference arise from improved automatization of gait, or improved ability to coordinate cognitive and motor tasks performed simultaneously. Therefore, the findings of this study will help clinicians make decisions about the types of activities to include in rehabilitation to improve dual-task walking after stroke.

We will measure the effects of the intervention not only on dual-task gait performance, but also on dual-task cognitive performance, which will reveal information about whether voluntary attention allocation changes over time: for example, whether improvements in dual-task gait performance occur at a cost to dual-task cognitive performance, or whether overall dual-task capacity appears to improve. Secondary outcome measures will provide important information about how DTGT and STGT impact locomotor control during obstacle avoidance, spontaneous physical activity in the community, and other measures of cognitive and motor impairment. This study will make an important and unique contribution to the evidence base for physical therapy rehabilitation post-stroke, because it explores the components of rehabilitation that can potentially minimize disabling dual-task interference in stroke survivors.

## Abbreviations

ANOVA: Analysis of variance; DTE: Dual-task effect; DTGT: Dual-task gait training; IRB: Institutional Review Board; MoCA: Montreal Cognitive Assessment; STGT: Single-task gait training.
